## Abstract

**Background:**

Lower back pain is a global health issue affecting approximately 80% of people at some stage in their life. The current literature suggests that any exercise is beneficial for reducing back pain. However, as pain is a subjective evaluation and physical deficits are evident in low back pain, using it as the sole outcome measure to evaluate superiority of an exercise protocol for low back pain treatment is insufficient. The overarching goal of the current clinical trial is to implement two common, conservative intervention approaches and examine their impact on deficits in chronic low back pain.

**Methods/design:**

Forty participants, 25–45 years old with chronic (>3 months), non-specific low back pain will be recruited. Participants will be randomised to receive either motor control and manual therapy (*n* = 20) or general strength and conditioning (*n* = 20) exercise treatments for 6 months. The motor control/manual therapy group will receive twelve 30-min sessions, ten in the first 3 months (one or two per week) and two in the last 3 months. The general exercise group will attend two 1-hour sessions weekly for 3 months, and one or two a week for the following 3 months. Primary outcome measures are average lumbar spine intervertebral disc T2 relaxation time and changes in thickness of the transversus abdominis muscle on a leg lift using magnetic resonance imaging (MRI). Secondary outcomes include muscle size and fat content, vertebral body fat content, intervertebral disc morphology and water diffusion measured by MRI, body composition using dual energy X-ray absorptiometry, physical function through functional tests, changes in corticospinal excitability and cortical motor representation of the spinal muscles using transcranial magnetic stimulation and self-reported measure of pain symptoms, health and disability. Outcome measures will be conducted at baseline, at the 3-month follow-up and at 6 months at the end of intervention. Pain, depressive symptomology and emotions will be captured fortnightly by questionnaires.

**Discussion:**

Chronic low back pain is ranked the highest disabling disorder in Australia. The findings of this study will inform clinical practice guidelines to assist with decision-making approaches where outcomes beyond pain are sought for adults with chronic low back pain.

**Trial registration:**

Australian New Zealand Clinical Trials Registry, ACTRN12615001270505. Registered on 20 November 2015.

**Electronic supplementary material:**

The online version of this article (doi:10.1186/s13063-017-1913-8) contains supplementary material, which is available to authorized users.

## Background

Low back pain is a global health issue affecting up to 84% of adults [1]. In Australia, it bears the greatest cost to society in terms of disability and lost productivity compared to any other disease [2]. Chronic non-specific lower back pain represents approximately 23% of reported low back pain; however, it consumes a large fraction of the $9.17 billion Australia spends annually on back pain [3, 4].

Meta-analysis has shown that whilst exercise in general is beneficial for reducing back pain [5], there is no clear evidence for superiority of one exercise protocol above another. As pain has been identified as multifactorial, a subjective method of measuring pain with ‘self-reported’ tools as the sole outcome to evaluate the superiority of a particular exercise protocol for chronic low back pain is insufficient. Other decrements can be measured to detect the effectiveness of a particular exercise protocol that would provide further information for the selection of treatment approaches for chronic low back pain. The overarching goal of the current randomised clinical trial is to implement two common, but distinct, conservative intervention approaches and examine their impact on a variety of deficits in chronic low back pain. This information will then contribute to guidelines for advising clinicians on expected physical, functional and psychological outcomes following each of these typical interventions for chronic low back pain.

Changes to the intervertebral discs (IVDs) of the lumbar spine are considered to be a common trigger for generating pain [6, 7], and back pain is associated with IVD degeneration [8–10]. Whilst we have an in-depth understanding of what loading protocols and activities might damage the IVD [11, 12], it is not clear whether habitual activities or exercise regimens lead to positive IVD adaptations. In a recent review of the literature, it was proposed that specific exercise and loading protocols might lead to an anabolic response in the IVDs [12]. Whilst there is research in animals to show that IVD anabolism can occur in response to ambulatory exercise [13], currently there is no compelling evidence that the IVDs can respond positively to exercise in humans. Recently, long-distance runners were found to have better IVD characteristics than non-athletes; however, this was tested only through a cross-sectional study [14]. A randomised controlled trial of exercise targeting the IVD is necessary to provide evidence as to whether the IVD can respond positively to exercise and what types of exercise might be optimal. Beyond feeding into guidelines for the prevention and management of IVD injury and spinal pain, this trial will address underlying questions of whether the IVD, similar to muscle [15] and bone [16], can positively respond to exercise. A primary aim of this study is to conduct a pilot study to examine whether a specially designed exercise protocol can result in positive adaptations in the lumbar IVDs.

The time required for a measurable response of the IVD to loading in humans is not clear. Given data indicating that adaptation of tendon tissue in humans requires a month or more [17], and that bone typically requires 6 months to 1 year before a measurable change in bone density in response to exercise can be detected [18, 19], we decided to implement a 6-month intervention period with follow-up at 3 and 6 months to track the time course of adaptation.

Beyond this, in chronic low back pain there is evidence of impaired motor functioning of specific trunk muscles. It has been previously acknowledged that the deep muscles of the trunk, in particular the transversus abdominis, provide an anatomical and biomechanical stiffness of the lumbar spine, potentially providing a protective effect to the spine [20–23]. The function of the transversus abdominis has been found to be negatively impacted in patients with low back pain. There is impaired ability to contract this muscle in athletic populations with back pain [24, 25] and also delay of its activation in postural adjustments [26]. This is thought to reduce stability within vertebral segments and predispose to future injury [25, 27]. There is little information in the literature, however, as to whether performing a targeted rehabilitation protocol restores the function of these deep muscles. Despite the number of cross-sectional studies suggesting a role of the transversus abdominis in back pain, we have identified only one randomised trial in which the effectiveness of specific muscle activation exercises on the function of the transversus abdominis was measured [28], and this study did not find evidence for efficacy of this training program for improving transversus abdominis muscle activation timing. There is evidently a paucity of data on whether the purported targets of specific motor control training are indeed achieved [29]. The second primary aim of this trial is to examine the impact of a specific motor control program on activation of the transversus abdominis in chronic low back pain.

Furthermore, a number of other deficits have been commonly identified in low back pain. Spinal muscle atrophy, strength loss [30–34], reduced activity levels [32, 35–37], reduced cardiovascular fitness [38, 39], muscular endurance and flexibility [40, 41] as well as decreased corticospinal excitability of the paravertebral muscles as measured by transcranial magnetic stimulation [42], poorer sleep quality [43], depressive symptoms [44] and fear of movement [45] have all been demonstrated in patients with low back pain and are thought to contribute to reductions in daily activity and chronicity of pain. With so many indicators of chronic lower back pain being identified, there is a scarcity of data in the literature as to whether various exercise protocols are more beneficial for improving these outcomes. For example, multifidus muscle size has shown both increases and decreases with exercise interventions [46–48], making it difficult to draw conclusions to inform clinical practice. The secondary aim of this study is to examine the impact of the exercise protocols on additional deficits of low back pain previously not measured, including muscle atrophy, physical function parameters, central nervous system adaptations and psychological factors in chronic low back pain.

## Methods/design

### Design

The randomised clinical trial is summarised in Fig. 1. The study was approved by the Deakin University Human Research Ethics Committee on 12 October 2015 and is registered with the Australian New Zealand Clinical Trials Registry (ACTRN12615001270505). Reporting of the study will adhere to the Consolidated Standards of Reporting Trials (CONSORT) guidelines [49]. Participants will be randomised into either a motor control and manual therapy treatment group or a general strength and conditioning group. The SPIRIT checklist for this study protocol can be accessed as Additional file 1.

**Fig. 1 Fig1:**
[figure not shown]
Trial flowchart outlining participant testing and intervention duration. Fortnightly questionnaires (indicated by *FQ*; depressive symptoms, pain, Positive and Negative Affect Schedule (*PANAS*)) are emailed throughout study. At baseline, 3-month and 6-month follow-up the following tests are performed: anthropometry, dual energy X-ray absorptiometry, VO_2_ peak, one-repetition maximum (*1RM*) muscular strength, 70% 1RM local muscular endurance (*LME*), Trunk LME, transcranial magnetic stimulation, magnetic resonance imaging, and questionnaires are given (Sports Injury Rehabilitation Beliefs Survey, International Physical Activity Questionnaire, medication, Oswestry Disability, Medical Outcome Trust Short Form-36 Health Survey V1, Pittsburgh Sleep, Tampa Kinesiophobia, Endicott Work Productivity, PANAS, depressive symptoms and pain)

### Participants

Volunteers aged 25–45 years [50] with non-specific chronic (>3 months) lower back pain between the T12 vertebra and the gluteal fold with a pain intensity from 2 to 8 (inclusive) on a numerical rating scale (NRS) of 0 to 10 will be eligible to participate in the study. The age range was restricted, as the response of IVD cells to loading depends [50] on whether these cells come from younger versus older or degenerated versus non-degenerated IVDs. The data [51–53] in the literature indicate that the IVD is still maturing in the third decade of life. Beyond approximately the age of 35, there is a normal age-related decline in IVD tissue, and IVD degeneration becomes more common [53]. Volunteers will be excluded from participation if they report a history of spinal surgery, history of traumatic injury to the spine (e.g. fractures, car accident), symptoms of cauda equina syndrome, planning or possibility of invasive treatment (surgery, injections) in the next 6 months, known structural scoliosis, symptoms of nerve root compression including radicular pain or pins/needles/numbness in a dermatomal distribution or non-musculoskeletal causes of back pain (as determined through magnetic resonance imaging (MRI) at baseline). They will also be excluded if they are unable to communicate easily in English, have current parallel treatment for back pain, report more than 150 min/week of moderate-vigorous exercise, participate in formal organised sport, participate in gym-based exercise more than one day per week, have a compensable claim for their back pain, are pregnant, possibly pregnant or considering pregnancy in the next 6 months, have given birth in the last 9 months, are currently breast-feeding, are a current smoker, have known anaemia, a body mass of more than 120 kg or a history (including familial history) of seizures or epilepsy, stroke, head injury or brain-related disorders, are on medication for mental illness, have metal implants or electronic implants unsuitable for MRI or dual energy X-ray absorptiometry (DXA), have had nuclear medicine (radioactive contrast agent) performed in the last 3 months or are unable to attend two 1-hour training sessions per week over a 6-month period and three 3-hour testing days plus an additional MRI scan.

### Recruitment

Participants will be recruited from the general public between inner Melbourne and the eastern suburbs. Print and web-based advertisements will be distributed to local businesses and medical/health centres, within Deakin University staff and students via email and posted on social media. A study website will be provided, and interested volunteers will be required to register through this website. Study team members will then make contact via telephone where applicants will be screened against inclusion and exclusion criteria and made aware of the study time frame and commitment. If the applicant passes telephone screening, he/she will be sent the study plain language statement consent form, explaining study requirements, procedures and time commitments, and will be required to visit a general practitioner (GP) to gain clearance to participate.

### Sample size

Prior data on the impact of interventional exercise on the intervertebral disc do not exist. Recent cross-sectional work on habitual (minimum 5-year history) runners and sedentary individuals showed a 9–11% difference in lumbar IVD T2-time between these collectives [14]. For this first interventional study on exercise and IVD adaptation, we targeted a 0.5% change in lumbar IVD T2-time as a minimum detectable effect size. This compares to a 0.2–0.3% loss of lumbar IVD T2-time per 1 year with normal aging above the age of 30 [54]. Data from the research group ([name] et al., unpublished observations) show a mean (SD) lumbar IVD T2-time of 100.6 (12.4) with a correlation of 0.982 (coefficient of variation (CV): 1.7%) between repeated measures. To detect a 0.5% difference, or an effect size of 0.0406, on a group*time interaction in the change in lumbar IVD T2-time with two study arms and three measurement time-points, and assuming an alpha of 0.05 and a power of 0.8, a sample size of 36 would be required. Assuming 10% dropouts, this implies a total pool of 40 participants would need to be included in the study. G*Power (version 3.1.2) [55] was used for these calculations.

In reviewing the literature, we were not able to identify data on the reliability of measurement of contraction of the transversus abdominis muscle on MRI (Fig. 3). The current study should be considered a pilot study for the impact of the motor control intervention for contraction of the transversus abdominis muscle on MRI.

For the secondary outcome of muscle size, data from our previous work of average lumbar multifidus cross-sectional area showed a correlation of 0.948 between repeated measures with a mean (SD) of 559 (72) mm^2^ [56]. With a total sample size of 36 participants, an effect size of 0.89% or 4.97 mm^2^ between groups (group*time interaction) should be detectable.

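### The sample size uses between-repeat correlations (0.982 for T2-time, 0.948 for multifidus) as if they held across 6 months of training, so the stated power is a best case

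*Protocol article*

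**What the plan says.** The Sample size section starts by acknowledging that "Prior data on the impact of interventional exercise on the intervertebral disc do not exist". It then takes a T2-time mean of 100.6 and SD of 12.4 from the group's unpublished observations, "with a correlation of 0.982 (coefficient of variation (CV): 1.7%) between repeated measures". The target is expressed as follows: "To detect a 0.5% difference, or an effect size of 0.0406, on a group*time interaction", "with two study arms and three measurement time-points". The result is that, "assuming an alpha of 0.05 and a power of 0.8, a sample size of 36 would be required", which becomes 40 after 10% dropout.

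The muscle-size outcome is handled in the same way: "data from our previous work of average lumbar multifidus cross-sectional area showed a correlation of 0.948 between repeated measures", with mean 559 and SD 72 mm², and a difference of 4.97 mm² (0.89%) said to be detectable with 36 participants.

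No other correlation is given. The section makes no allowance for differences in individual response and shows no sensitivity analysis.

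**The concern.** A power routine for a group-by-time interaction needs the correlation between visits within an arm while participants train. A correlation between repeated measures in people who are not being trained contains measurement error and perhaps natural drift. It does not contain differences between people in how much their discs or muscles respond. Entering it assumes that everyone in an arm changes by the same amount.

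The noncentrality parameter scales with 1/(1 − r), so close to r = 1 a small fall in r costs much power. T2-time is a primary outcome, and its calculation is the only one that sets N. If the 80% claim stands unqualified, a null T2-time result could be read as showing that discs do not adapt to exercise.

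**Working it through.** **Inputs** (Sample size section): T2-time mean 100.6, SD 12.4, r = 0.982; effect size 0.0406; 2 arms; 3 visits; alpha 0.05; N = 36. Multifidus: mean 559, SD 72, r = 0.948, difference 4.97 mm².

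**1. Reproducing the plan's figure.** For the within-between interaction, λ = f²·N·m/(1 − r), with (2 − 1)(3 − 1) = 2 and (36 − 2)(3 − 1) = 68 degrees of freedom.

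λ = 0.0406² × 36 × 3 / 0.018 = 9.89, giving power 0.792.

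Power is 0.804 at N = 37, so 36 is reproduced to within rounding. Multifidus follows the same recipe: f = 4.97/72 = 0.0690, λ = 9.90, power 0.793. In both cases the between-repeat correlation is used as the correlation across the three visits.

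**2. What r = 0.982 leaves for individual response.** Within-person SD = 12.4 × √(1 − 0.982) = 1.66, or 1.65% of 100.6. SD of change between two visits = 12.4 × √(2 × 0.018) = 2.353. All of this is variation between repeats; none is left for differing responses to training.

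**3. Adding true differences in change.** Let s be the SD of true change, independent of measurement error. The documents give no value, so the range is assumed. Var(change) = 2.353² + s², and the approximate effective r = 1 − Var(change)/(2 × 12.4²). With f = 0.0406 and N = 36 unchanged:

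| s (% of 100.6) | SD of change | Effective r | Power on the plan's inputs |
|---|---|---|---|
| 0 | 2.353 | 0.982 | 0.79 |
| 0.5 | 2.406 | 0.981 | 0.77 |
| 1 | 2.559 | 0.979 | 0.72 |
| 2 | 3.096 | 0.969 | 0.54 |
| 3 | 3.827 | 0.952 | 0.38 |

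For multifidus, r = 0.90 in place of 0.948 takes power from 0.79 to 0.50.

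**4. These powers inherit a scaling error.** 0.5% of 100.6 is 0.503, and 0.503/12.4 = 0.0406. That is a standardised mean difference, but the routine treats it as Cohen's f. Suppose the 0.503 between-arm difference is present at 3 months and held. The half-differences centred over visits are −0.168, 0.084 and 0.084; their root mean square is 0.1186, so f = 0.1186/12.4 = 0.0096 and power at r = 0.982 is 0.09. A two-sample t test on change (18 per arm, SD 2.353) gives 0.10. The table in step 3 therefore shows only how sensitive the plan's own claim is to r. It does not give the trial's actual power.

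**5. Detectable difference from the SD of change.** With 18 per arm and 34 degrees of freedom, 80% power at two-sided 0.05 needs a noncentrality of 2.884. Detectable difference = 2.884 × √(2/18) × SD of change = 0.961 × SD of change.

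| Outcome | Assumption | SD of change | Detectable difference |
|---|---|---|---|
| T2-time | s = 0 (r = 0.982) | 2.353 | 2.26 (2.2%) |
| T2-time | s = 1% | 2.559 | 2.46 (2.4%) |
| T2-time | s = 2% | 3.096 | 2.98 (3.0%) |
| T2-time | s = 3% | 3.827 | 3.68 (3.7%) |
| Multifidus | r = 0.948 | 23.2 mm² | 22.3 mm² (4.0%) |
| Multifidus | r = 0.90 | 32.2 mm² | 31.0 mm² (5.5%) |

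A model using both follow-ups can do somewhat better. If the effect is the same at both, errors are independent and s = 0, averaging the follow-ups multiplies the SD of change by √(1.5/2) = 0.87. That brings 2.2% down to about 1.9%, still well above 0.5%.

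**The case against.** Several stronger readings are tempting, and the documents do not support them.

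- **That 0.982 is proven to be short-term repeatability.** A reader might infer this from the match between 1.65% and the quoted CV of 1.7%. For a given mean and SD, r and the CV express the same within-person variance, so they would agree whatever the interval. The interval is not stated and the T2 source is unpublished. What stands is narrower: the T2 value cannot describe discs under an exercise intervention. That argument does not carry over to 0.948, whose cited source is not shown; the only evidence there is that it is described as a correlation between repeated measures.
- **That the protocol contradicts equal response.** The Participants section says the age range was limited, "as the response of IVD cells to loading depends [50] on whether these cells come from younger versus older". This explains an eligibility rule meant to reduce variation, and it concerns cells. It makes some residual variation among 25- to 45-year-olds plausible but gives no size for it.
- **That power collapses to 20% or 12%.** Those figures need r = 0.90 or 0.80, which imply true-change SDs of about 5.0% and 7.4%. The protocol cites ageing loss of 0.2–0.3% a year, and 9–11% between sedentary people and runners of at least 5 years. Nothing in it supports SDs that large over 6 months. If s equals the 0.5% target, the loss is two points.
- **That the correlation is why 80% power is missed.** Once the effect is put on the right scale, power at 0.5% is about 10% with no individual variation at all.

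It is also fair to say that the Background calls the disc question a pilot, and that the protocol nowhere claims a null result would exclude an effect. The Sample size section still states 80% power at 0.5%, and its pilot caveat is attached to transversus abdominis, not to T2-time.

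**Conclusion.** The point holds in a limited form. The stated power rests on a correlation that makes no allowance for differing responses to training, so 0.982 is a ceiling; 0.948 should be labelled likewise. Provided true change is independent of measurement error, any spread in response lowers power. How much is unknown: the loss is small at a true-change SD of 0.5% (0.79 to 0.77), modest at 1% (0.72), and large only at 2% or more (0.54 at 2%, 0.38 at 3%). The effective-r mapping is approximate, because individual trends over three visits do not give equal correlations.

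The detectable differences are the more useful result because they avoid the scaling error: about 2.2% to 3.7% for T2-time over an SD of 0 to 3%, against a 0.5% target. Correcting the correlation alone would not repair the calculation.

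**What to change.** In the Sample size section:

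- Keep N = 40.
- State the retest interval behind 0.982 and 0.948 and label both as best-case values.
- Replace the single 80% statement with the between-arm difference in change detectable with 36 completers, over a true-change SD of, for example, 0 to 3%, or over a range of r.
- Compute this from the SD of change, not from 0.0406 (or 4.97/72) entered as Cohen's f.
- Add a sentence that a non-significant T2-time result does not exclude a 0.5% difference.

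The cost is one recalculation and the rewording of one section. No participants, visits or procedures are added, but the stated sensitivity becomes less favourable.

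### The sample size of 36 reproduces only if a standardised mean difference (0.0406) is used as Cohen's f; power for the stated 0.5% T2 difference is about 8–10%, not 80%

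*Protocol article*

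**What the plan says.** The Sample size section of the protocol article sets the target for the first primary outcome: "we targeted a 0.5% change in lumbar IVD T2-time as a minimum detectable effect size". Its planning data, a mean with its SD in brackets, come from unpublished work of the group: "lumbar IVD T2-time of 100.6 (12.4) with a correlation of 0.982 (coefficient of variation (CV): 1.7%) between repeated measures". The purpose of the calculation is given as "To detect a 0.5% difference, or an effect size of 0.0406, on a group*time interaction in the change in lumbar IVD T2-time". The design entered has both arms and all three visits, and the result reads: "assuming an alpha of 0.05 and a power of 0.8, a sample size of 36 would be required". Allowing 10% dropout gives 40, and G*Power 3.1.2 is named as the software. The Statistical analysis section confirms that the group-by-time interaction from a mixed model is the test of interest, at the 0.05 level.

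The same section says that 36 participants suffice to detect a multifidus difference of 4.97 mm² (0.89%), given SD 72 mm² and correlation 0.948. For transversus abdominis contraction, the other primary outcome, no power is calculated. The T2 statement is therefore the only power statement for a primary outcome.

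**The concern.** An effect size of 0.0406 is a difference of half a T2 unit set against an SD of 12.4. Even with a very high correlation between visits, 18 people per arm cannot be expected to resolve so small a difference. The term effect size is also used without saying which one. A difference divided by an SD is on the scale of Cohen's d. An interaction F test in repeated-measures ANOVA is powered on Cohen's f, the SD of the interaction cell effects divided by the within-cell SD. For this design f is less than a quarter of d, so using one for the other inflates the noncentrality by a factor of 18 to 24.

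At stake is the reading of the trial. If 0.5% is accepted as detectable with 80% power, a non-significant result invites the conclusion that even a 0.5% effect on the disc is unlikely. The article's Discussion expects the results to guide treatment decisions.

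**Working it through.** **Inputs** (all from Sample size in the protocol article): mean 100.6, SD σ = 12.4, correlation ρ = 0.982, target 0.5%, k = 2 arms, m = 3 visits, α = 0.05, N = 36 completers. The abstract gives 20 per arm randomised, so 18 per arm complete.

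**1. What 0.0406 is.** 0.005 × 100.6 = 0.503 units; 0.503 / 12.4 = 0.0406. This is d.

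**2. Reproducing the article's N.** For the within-between interaction, λ = f²·N·m/(1−ρ), with df₁ = (k−1)(m−1) = 2 and df₂ = (N−k)(m−1) = 68.
- f = 0.0406: λ = 0.0406² × 36 × 3 / 0.018 = 9.89, power 79.2%.
- f = 0.041: power 80.06%.

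So 36 is recovered, to rounding, when 0.0406 stands in for f.

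**3. Second check, multifidus.** 4.97 / 72 = 0.0690. Used as f with ρ = 0.948 and N = 36, λ = 9.90 and power is 79.3%. Two separate figures fit the same reading.

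**4. Correct f.** Let δⱼ be the between-arm difference in change at visit j, in SD units. The interaction cell effects are ±(δⱼ − δ̄)/2, so f = ½·√[mean of (δⱼ − δ̄)²].
- Full difference at both follow-ups (0, d, d): the mean square is (2/9)d², so f = d/4.24 = 0.0096.
- Linear build-up (0, d/2, d): the mean square is (1/6)d², so f = d/4.90 = 0.0083.

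**5. Power for 0.5% with 36 completers.**

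| Test | Power |
|---|---|
| Interaction, linear pattern (λ = 0.41) | 8.1% |
| Interaction, step pattern (λ = 0.55) | 9.2% |
| t test on 6-month change | 9.6% |
| Mean of both follow-ups minus baseline | 11.1% |

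The change-score test needs no f at all. SD of change = 12.4 × √(2 × 0.018) = 2.353; SE for 18 v 18 = 2.353 × √(2/18) = 0.784; 0.503 / 0.784 = 0.64 standard errors. The stated CV gives nearly the same: 0.017 × 100.6 × √2 = 2.42, power 9.3%.

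**6. What 36 completers can detect with 80% power.**
- 6-month change: 2.26 units, or 2.26 / 100.6 = 2.2%.
- Interaction: 2.16 units (2.1%, step) to 2.49 units (2.5%, linear).
- Expected 95% CI half-width for 6-month change: 2.03 × 0.784 = 1.59 units, or 1.6%.
- For 0.5%: 345 completers per arm (t test on change), or 634 to 846 in total (interaction).

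**7. Sensitivity to the correlation (assumed values).** At ρ = 0.95 the SD of change is 12.4 × √0.10 = 3.92 and the detectable difference is 3.7%. At ρ = 0.90 it is 12.4 × √0.20 = 5.55 and 5.3%.

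**8. Multifidus, corrected.** The f needed for 80% power is 0.04097 × √(0.052/0.018) = 0.0696. Multiplying by 4.24 to 4.90 and by 72 gives 21.3 to 24.6 mm², or 3.8% to 4.4% of 559 mm², against the 4.97 mm² stated.

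**The case against.** - **The mechanism is inferred.** The article does not name the G*Power routine or say whether 0.0406 is d or f, and 0.0406 gives 79.2% at N = 36, not exactly 80%. That is so, but the finding does not depend on the mechanism. The change-score check in step 5 shows directly that 36 completers cannot give 80% power for 0.503 units.
- **A kinder reading of the target is possible.** If each arm moves 0.5% in opposite directions, so that they end 1% apart, interaction power is 19% to 24%. Halving d to obtain f (0.0203) gives 26%. Neither approaches 80%.
- **The correlation may be sound.** The article calls 0.982 a correlation between repeated measures and gives no interval. The CV fits it as measurement error: 12.4 × √0.018 / 100.6 = 1.65%, against 1.7% stated. That does not prove that it is a short-term repeatability figure, so doubt about its use over 6 months is a caveat, and 0.95 and 0.90 are assumptions only. The main result uses 0.982 as given.
- **The trial is a pilot.** Background calls the disc aim a pilot, no earlier interventional data existed, and a detectable 2.1% to 2.5% is still well below the 9–11% cross-sectional difference cited for runners. This supports keeping N = 40. It does not make a formal claim of 80% power correct.
- **No exclusion rule is stated.** The article sets no equivalence or futility criterion, so misreading a null result is a risk of interpretation, not a planned step.

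**Conclusion.** The concern holds. The printed power and minimum detectable effect for disc T2-time are wrong on the article's own inputs. Power for a 0.5% between-arm difference is about 8% to 10% with 36 completers (8.5% to 10.1% if all 40 complete), and 11% for the most favourable contrast examined. The difference detectable with 80% power is about 2.1% to 2.5%, four to five times what is stated. This rests on equal correlations between visits, sphericity, 18 completers per arm, a two-sided 5% test, and 0.982 holding over 6 months; a lower 6-month correlation makes matters worse. The statement must be corrected, because it is the only power statement for a primary outcome. The multifidus figure needs the same correction.

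**What to change.** Keep 40 participants and replace the T2 statement with wording such as: *With 36 completers, the trial has 80% power to detect a between-arm difference in 6-month change in lumbar disc T2-time of about 2.2% (2.1% to 2.5% for the group-by-time interaction, depending on its pattern), assuming SD 12.4 and a correlation of 0.982 between visits. Power for a 0.5% difference is about 10%. A non-significant result does not exclude a 0.5% change.*

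Remove 0.5% as the minimum detectable effect. Say over what interval the correlation of 0.982 was observed; if it is short-term repeatability, add the sensitivity figures, labelled as assumptions (3.7% at 0.95, 5.3% at 0.90). Restate the multifidus figure as about 21 to 25 mm² (3.8% to 4.4%) on its stated SD and correlation. Name the effect-size measure wherever one is given.

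The cost is wording only: no extra participants, and no change to design, outcomes or analysis. The stated sensitivity of the trial becomes less favourable. Since recruitment was still under way when the article was submitted, the correction belongs in the analysis plan and the results report as well.

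### The stated detectable multifidus difference (0.89%, 4.97 mm²) is about 4.5 times too small: an interaction effect size f appears to have been read as a standardised mean difference

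*Protocol article*

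**What the plan says.** The Sample size section of the protocol article takes its multifidus inputs from the group's earlier work: "a correlation of 0.948 between repeated measures with a mean (SD) of 559 (72) mm^2". It then says: "With a total sample size of 36 participants", "an effect size of 0.89% or 4.97 mm^2^ between groups (group*time interaction) should be detectable".

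The design settings appear only in the preceding paragraph, on disc T2-time: an interaction test "with two study arms and three measurement time-points", "assuming an alpha of 0.05 and a power of 0.8, a sample size of 36 would be required". The effect size there is introduced as "To detect a 0.5% difference, or an effect size of 0.0406, on a group*time interaction". G*Power 3.1.2 is named as the software. The Statistical analysis section plans mixed models testing group × time at the 0.05 level for all continuous outcomes.

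**The concern.** The claim looks implausible before any formal power calculation. A correlation of 0.948 with an SD of 72 mm² implies that individual changes vary with an SD of about 23 mm². With 18 people per arm, the standard error of the between-arm difference in change is close to 8 mm². A difference of 4.97 mm² is less than one standard error, and 80% power needs nearly three.

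Muscle size is the only secondary outcome given a sensitivity statement. The Background notes that exercise trials have shown multifidus size moving in both directions, and the motor control programme names multifidus as a target muscle. A reader who relied on the stated figure could take a null multifidus result as evidence against a difference of about 1%, when the trial is sized to detect about 4%.

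**Working it through.** **Inputs.** From the Sample size section: mean 559 mm², SD 72 mm², correlation ρ = 0.948, N = 36. From the abstract: equal allocation, hence 18 per arm. From the T2-time paragraph and assumed to carry over: two arms (k = 2), three visits (m = 3), α = 0.05, power 0.80. Compound symmetry is also assumed.

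**1. Reproducing the stated figure.** For a repeated-measures within–between interaction, λ = f²·N·m/(1−ρ), with (k−1)(m−1) = 2 and (N−k)(m−1) = 68 degrees of freedom.

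- Stated effect over SD: 4.97/72 = 0.0690.
- Entered as f: λ = 0.0690² × 36 × 3/0.052 = 9.90, giving power 79.3%.
- Solving for exactly 80% gives f = 0.0696, and 0.0696 × 72 = 5.01 mm² (0.90%).

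The T2-time calculation behaves the same way. Its effect size is 0.005 × 100.6/12.4 = 0.0406, a raw difference divided by an SD. Entered as f with ρ = 0.982 and N = 36, it gives power 79.2%. Rescaling it to the multifidus inputs gives 0.0406 × √(0.052/0.018) × 72 = 4.97 mm², exactly the printed value.

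**2. What f means as a difference between arms.** Let D be the between-arm difference in change at its full size. At each visit the two arms' interaction effects are ± half the deviation of the between-arm difference from its mean over visits, and f is the root mean square of these effects divided by the SD.

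- Linear growth (0, D/2, D): effects ∓D/4, 0, ±D/4; mean square D²/24; so D = √24·f·SD = 4.90·f·SD.
- Full effect from 3 months (0, D, D), or only at 6 months (0, 0, D): mean square D²/18; so D = √18·f·SD = 4.24·f·SD.

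**3. Power at a true 4.97 mm².**

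| Test | Calculation | Power |
|---|---|---|
| Interaction, linear | f = 0.0690/4.90 = 0.0141 | 8.1% |
| Interaction, step | f = 0.0690/4.24 = 0.0163 | 9.2% |
| t test on 6-month change | SD of change = 72 × √(2 × 0.052) = 23.2; SE = 23.2 × √(2/18) = 7.74; 4.97/7.74 = 0.64 SE | 9.6% |

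Simulating the interaction test (20,000 runs, 18 per arm) gave 7.6% for the linear course and 9.2% for the step.

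**4. Difference detectable with 80% power.**

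| Test | Difference | % of 559 | Ratio to 4.97 |
|---|---|---|---|
| Interaction, step | √18 × 0.0696 × 72 = 21.3 mm² | 3.8% | 4.3 |
| t test on 6-month change | 22.3 mm² | 4.0% | 4.5 |
| Baseline-adjusted 6-month comparison (ANCOVA) | 22.0 mm² | 3.9% | 4.4 |
| Interaction, linear | √24 × 0.0696 × 72 = 24.6 mm² | 4.4% | 4.9 |

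**5. Variants.** Using N = 34, 38 or 40 moves f × SD only to 5.17, 4.87 or 4.75 mm²; two visits give 5.58 mm². These change which f is detectable, but f × SD is still not a difference between arms. A one-sided test on 6-month change would still need about 19 mm². Averaging the two follow-ups, which is not the stated test, still leaves a factor of about 3.8 to 3.9.

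**The case against.** Five points can be made for the plan.

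- **The cause is inferred.** No f and no software output are printed for multifidus. That is so, and the explanation should be worded as what appears to have happened. But the rescaled T2-time entry returns 4.97 to the last digit, and the figure is too small whatever its origin.
- **4.97 mm² might be meant as the spread of interaction effects (f × SD).** The sentence calls it an effect between groups and gives it as a percentage, so a reader has no reason to take it that way.
- **The size of the error depends on assumptions.** The factor runs from 4.3 to 4.9 for the interaction test, under compound symmetry and the settings carried over from T2-time. This stands as a reason to give a range. No variant tried brings the factor near 1, and a 6-month correlation below 0.948 would make the detectable difference larger.
- **A single replacement of 22 mm² does not match the planned test exactly.** On the interaction test, 22 mm² has about 70% power under linear growth and 83% under a step. This also stands, and bears on the wording of the correction.
- **The consequence is modest.** Multifidus size did not set N, the same root error affects the T2-time calculation that did, and the article states no rule for interpreting a null result. This limits priority but does not make the printed figure right.

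**Conclusion.** The concern holds. On the protocol's own inputs, the trial with 36 participants has 80% power for a between-group difference in multifidus change of about 22 mm² (4%), or 21.3 to 24.6 mm² (3.8–4.4%) on the group-by-time test. The stated 4.97 mm² (0.89%) is too small by a factor of about 4.3 to 4.9, and a true difference of that size would be missed about nine times in ten.

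This rests on α = 0.05, 80% power and three visits carrying over from the T2-time paragraph, and on a constant correlation of 0.948 over 6 months. It should be corrected, but it is an overstated sensitivity claim for a secondary outcome and not a fault in how N was set for that outcome.

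**What to change.** Replace the multifidus sentence with wording such as: *With 36 participants, a between-group difference in change of about 22 mm² (4%) at 6 months is detectable with 80% power at a two-sided 0.05 level; for the group-by-time test over three visits the corresponding figure is 21 to 25 mm² (3.8–4.4%), depending on the time course of the effect.* State the assumed correlation and visit structure next to it.

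The cost is one sentence and a less favourable figure. For this outcome, no visit, analysis or recruitment number changes. The T2-time effect size in the same section should be revisited at the same time, because it follows the same pattern.
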